# Rivaroxaban compared to no treatment in ER-negative stage I–III early breast cancer patients (the TIP Trial): study protocol for a phase II preoperative window-of-opportunity study design randomised controlled trial

**DOI:** 10.1186/s13063-020-04675-7

**Published:** 2020-08-27

**Keywords:** Tissue Factor, Thrombin, FXa, DOAC, NOAC, Rivaroxaban, Breast cancer, Clinical trial, Ki67

## Abstract

**Background:**

Breast cancer patients are at a four-fold increased risk of developing a venous thromboembolism (VTE), a major cause of death in this group. Conversely, coagulation factors promote tumour growth and metastasis. This has been evidenced in preclinical models, with an inhibitory effect of anticoagulants on cancer growth through proliferative, angiogenic, apoptotic, cancer stem cell and metastatic processes. The extrinsic clotting pathway is also more upregulated in patients in the relatively poorer prognosis oestrogen receptor (ER)-negative breast cancer subgroup, with increased tumour stromal expression of the coagulation factors Tissue Factor and thrombin.

Rivaroxaban (Xarelto®, Bayer AG, Leverkusen, Germany) is a direct oral anticoagulant (DOAC). It is a Factor Xa inhibitor that is routinely prescribed for the prevention of stroke in non-valvular atrial fibrillation and for both VTE prophylaxis and treatment. This trial will assess the anti-proliferative and other anti-cancer progression mechanisms of Rivaroxaban in ER-negative early breast cancer patients.

**Methods:**

This UK-based preoperative window-of-opportunity phase II randomised control trial will randomise 88 treatment-naïve early breast cancer patients to receive 20 mg OD Rivaroxaban treatment for 11 to 17 days or no treatment. Treatment will be stopped 24 h (range 18–36 h) prior to surgery or repeat core biopsy. All patients will be followed up for 2 weeks following surgery or repeat core biopsy.

The primary endpoint is change in tumour Ki67. Secondary outcome measures include tumour markers of apoptosis and angiogenesis, extrinsic clotting pathway activation and systemic markers of metastasis, tumour load and coagulation.

**Discussion:**

Laboratory evidence supports an anti-cancer role for anticoagulants; however, this has failed to translate into survival benefit when trialled in patients with metastatic disease or poor prognosis cancers, such as lung cancer. Subgroup analysis supported a potential survival benefit in better prognosis advanced disease patients. This is the first study to investigate the anti-cancer effects of anticoagulants in early breast cancer.

**Trial registration:**

UK National Research Ethics Service (NRES) approval 15/NW/0406, MHRA Clinical Trials Authorisation 48380/0003/001-0001. The sponsor is Manchester University NHS Foundation Trust, and the trial is co-ordinated by Cancer Research UK Liverpool Cancer Trials Unit (LCTU). EudraCT 2014-004909-33, registered 27 July 2015. ISRCTN14785273.

## Background

Breast cancer in women is associated with a four-fold increased risk of venous thromboembolism (VTE) compared to age-matched women without cancer [1, 2]. Chemotherapy-induced VTE occurs in up to 7% of early breast cancer and 17% of metastatic breast cancer patients [3]. Breast cancer patients who develop VTE have a worse survival, which cannot solely be accounted for by VTE-induced mortality [4, 5]. It is thought to in part be due to a promotion of cancer growth and metastasis by coagulation factors.

Tissue Factor (TF), a transmembrane glycoprotein, is the initiator of the extrinsic clotting cascade. TF binds to plasma factor VII/VIIa (FVII/VIIa) to initiate coagulation via activation of Factor X (FX). This leads to the generation of thrombin, fibrin deposition and clot formation, as well as platelet activation (Fig. 1). In addition to its haemostatic role, TF activates cell signalling through TF:FVIIa and TF:FVIIa:FXa cleaving of the G-coupled protease-activated receptor (PARs) 1 and 2 complexes.

**Fig. 1 Fig1:**
[figure not shown]
The extrinsic coagulation pathway. Tissue Factor (TF), the main initiator of the coagulation cascade, complexes with Factor VIIa to activate Factor X, and in turn converts prothrombin (PT) to thrombin (Th) and ultimately fibrinogen to fibrin, with subsequent clot formation. FXa is inhibited by the direct oral anticoagulant Rivaroxaban. Thrombin also binds to protease-activated receptor 1 (PAR-1), and the TF/FVIIa/Xa complex to PAR-2. In cancer cells, this is proposed to result in pro-angiogenic, pro-proliferative and pro-invasive gene expression resulting in increased metastases. Figure created with BioRender.com [6]. Abbreviations: TF, Tissue Factor; FVIIa, activated Factor VII; FX, Factor X; FXa, activated Factor X; PT, prothrombin; Th, thrombin; PAR, protease-activated receptor

TF directly promotes tumour growth, migration and angiogenesis via activation of the PAR-2 receptor [7–11]. Thrombin can also modify tumour cell behaviour, directly through the activation of PAR receptors, indirectly by acting on stromal cells, or by the generation of fibrin matrices [12–14]. Thrombin promotes tumour growth in vitro [15] and in vivo [16–18], enhances tumour adhesion to platelets [16, 17, 19] and endothelial cells [20] in vitro and increases experimental (tail-vein injection) metastasis [16, 17, 19, 21]. Thrombin also increases tumour cell motility [22]. TF [23] and thrombin [24] promote neo-angiogenesis via upregulation of VEGF (a potent angiogenic factor) in cancer cells through the PI3K/Akt pathway [25]. TF also downregulates anti-angiogenic factors such as thrombospondin-1 and thrombospondin-2 [26], while thrombin upregulates matrix metalloproteinase-2 [27]. TF and thrombin also activate angiogenesis by clotting-dependent mechanisms through production (via thrombin) of polymerised fibrin which provides a scaffold around tumours to support and stimulate endothelial cell proliferation [28]. In clinical studies, TF expression correlates with VEGF expression and markers of angiogenesis [29], while prothrombin fragments (produced when prothrombin is converted to active thrombin) closely associate with areas of neo-angiogenesis at the tumour-stroma interface [30, 31].

Cancer cells express high levels of TF, thrombin and PARs [32, 33]. Breast cancer expression of TF has been reported to be an independent predictor of overall survival [34]. Plasma D-dimer (fibrin degradation by-product) is increased in breast cancer and correlates with tumour stage, poor prognosis molecular phenotypes oestrogen receptor (ER) negative, human epidermal growth factor receptor 2 (HER-2) positive [35, 36], circulating tumour cells [37, 38] and reduced survival [39]. D-dimer also has potential as a pharmacodynamic biomarker for chemotherapy response [40].

In a prospective cohort study of 248 early breast cancer patients, we found that tumour fibroblast expression of TF was increased in patients with primary breast cancer as compared to both ductal carcinoma in situ (DCIS) and normal breast. We also found that fibroblast TF, thrombin, PAR-1 and PAR-2 expression were increased in patients with ER-negative, HER-2-positive and high Ki67 tumours [41].

Inhibition of this coagulation cascade could therefore be a therapeutic option in breast cancer patients. A Cochrane review in 2011 reported that parenteral anticoagulation (with either unfractionated heparin or low molecular weight heparin) for patients with cancer, who have no therapeutic or prophylactic indication for anticoagulation, resulted in a statistically and clinically significant reduction in mortality at 24 months. This demonstrates a potential anti-cancer effect of anticoagulants in patients with better prognosis metastatic disease [42].

Direct oral anticoagulants (DOACs) inhibit thrombin (e.g. dabigatran etexilate (Pradaxa®)) or its activating enzyme Factor Xa (e.g. Rivaroxaban). DOACs have come into regular clinical use in the last decade for the prevention of VTE in orthopaedic surgery and of stroke in non-valvular atrial fibrillation [43, 44]. DOACs are also used for the treatment of primary or recurrent VTE. DOACs target a specific single enzyme within the extrinsic clotting pathway unlike the more widespread effects of heparins and vitamin K antagonists (Warfarin). A meta-analysis of randomised controlled trials of VTE-treatment with DOACs in cancer patients has indicated they are as safe and effective as conventional treatments [45].

Rivaroxaban was the first orally active direct Factor Xa inhibitor and, through inhibition of the Tissue Factor-Factor VIIa-Factor Xa complex, inhibits the conversion of prothrombin to thrombin [46]. Rivaroxaban is well absorbed from the gut and maximum inhibition of Factor Xa occurs 1 to 4 h after administration [47, 48]. Rivaroxaban has shown comparable safety to heparin for thromboprophylaxis after total hip replacements, with the convenience of oral dosing and reduced coagulation monitoring [49]. Rivaroxaban has the potential to downregulate the TF-FVIIa-FXa complex activation of PAR-2 and the subsequent tumour cell migration and production of pro-angiogenic and immune-modulating cytokines, chemokines and growth factors [10]. Rivaroxaban was chosen as the DOAC for this window-of-opportunity study as it inhibits the coagulation cascade at its origin and has a good safety profile. We have also found that Rivaroxaban inhibits cancer stem cell (CSC) activity in the in vitro functional CSC assay of mammosphere formation [50].

In summary, in vitro and in vivo evidence supports a potential inhibitory effect of anticoagulants on cancer growth through proliferative, cancer stem cell, angiogenic and metastatic processes. ER-negative early breast cancer patients have a relatively poorer prognosis and higher stage at diagnosis with an associated reduced disease-free survival. ER-negative early breast cancer patients also have fewer options for adjuvant therapy. Our previous data supports the hypothesis that the extrinsic clotting pathway is more upregulated in the ER-negative breast cancer subgroup as compared to ER-positive breast cancer, and thereby provides a potential therapeutic strategy.

To test a novel therapy in the adjuvant breast cancer setting would require thousands of patients, long follow-up and great expense. The alternative is the more novel ‘window-of-opportunity’ clinical trial design where drugs are tested over a short period, in the preoperative setting. Biomarkers are used as early markers for response and long-term outcome. Ki67 (tumour proliferation marker) is recognised as such a marker in trials of endocrine therapy. Short-term neoadjuvant studies have demonstrated that only 2 weeks of preoperative endocrine therapy induces changes in Ki67 which predicts for treatment benefit and long-term survival outcome [51]. By using biomarkers, we may be able to demonstrate the potential effectiveness of an anticoagulant in the clinical setting to support future larger adjuvant trials.

The TIP Trial will assess the anti-proliferative and other anti-cancer progression mechanisms of Rivaroxaban in ER-negative early breast cancer patients.

## Methods

This study protocol has been reported in accordance with the Standard Protocol Items: Recommendations for Clinical Interventional Trials (SPIRIT) guidelines (Additional file 1).

### Aim

The primary aim of the Thrombin Inhibition Preoperatively in Early Breast Cancer (TIP) trial is to determine whether preoperative administration of the oral Factor Xa inhibitor Rivaroxaban results in inhibition of tumour proliferation markers, as determined by a reduction in tumour Ki67 from baseline (pre-treatment) to post treatment (‘end-of-trial’, at time of surgical excision or repeat core biopsy prior to neoadjuvant chemotherapy), in ER-negative early breast cancer patients.

### Study design

The TIP trial is a phase II preoperative window-of-opportunity randomised controlled trial of Rivaroxaban compared to no treatment in ER-negative stage I–III early breast cancer patients.

This UK-based multi-centre study will randomise 88 eligible patients (1:1) to either Rivaroxaban 20 mg once daily (OD) or no treatment (control). Randomisation will be blinded to pathologists and data analysts, but not to patients or clinicians.

### Sample size calculation

The trial is designed with a two-sided alpha level of 0.05 and an estimated 80% power to detect a 0.6 standard deviation (SD) reduction in percentage tissue expression of Ki67 in early breast cancer patients treated with Rivaroxaban. Based on a two-sample *t* test with this 80% power, 88 eligible patients are required. We will allow for a 10% drop out rate, and therefore, 8 extra patients (giving a total of 96 patients) may need to be recruited. Any patient that withdraws from the trial or does not have surgery or a repeat core biopsy following treatment will be removed from the study and replaced.

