### Analysis

Both primary and secondary analyses will be carried out on an intention to treat (ITT) basis. Missing data or missing patients’ samples will be minimised by active monitoring by the Trial Coordinator, regularly reviewed by the Trial Management Group (TMG), including scheduled data cleaning, sample checking and communications with trial sites. If samples for the primary endpoint analysis are not collected, the patient will be replaced. Any patients who withdraw from the trial will be replaced. If the level of missing data exceeds these safeguards, it may be handled by multiple imputation. Separate multiple imputations by treatment arm would be performed, using the method of chained equations.

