### Participant retention and complete follow-up

The Trial Coordinator will produce reports on patient withdrawals, losses to follow-up and the quantity of missing CRFs/data across sites for review by LCTU business meetings, the Trial Management Group (TMG), Trial Steering Committee (TSC) and Independent Safety and Data Monitoring Committee (ISDMC). Any problems identified will be discussed and remedial action taken as necessary. Patients who withdraw from the trial will be replaced, and any who deviate will be managed on a case-by-case basis.

If a patient wishes to withdraw from trial treatment, this will be acted upon immediately and will cause no detrimental effect to them in receiving usual standard of care. Following end of study biopsy, a single safety follow-up is performed at ~ 2/52. There is no long-term follow-up within the trial. All long-term follow-up will be as per usual NHS practice.

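### The analysis is called intention to treat, but randomised patients without end-of-trial tissue are removed and replaced, so the analysed set is a completers (modified ITT) set

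*Protocol article*

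**What the plan says.** The protocol article makes two kinds of statement about who is analysed.

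- **Analysis principle.** Analysis section: "Both primary and secondary analyses will be carried out on an intention to treat (ITT) basis".
- **Removal and replacement.** Sample size calculation: a patient who withdraws from the trial or "does not have surgery or a repeat core biopsy following treatment will be removed from the study and replaced". Analysis: "If samples for the primary endpoint analysis are not collected, the patient will be replaced", with the same rule for withdrawals. Participant retention and complete follow-up: "Patients who withdraw from the trial will be replaced, and any who deviate will be managed on a case-by-case basis".

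The Analysis section also names multiple imputation by arm using chained equations. It is optional, and it comes into play only if missing data go beyond the preceding safeguards, which include replacement.

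Three other statements bear on the point. Pathologists, laboratory staff and analysts are blinded, but patients and clinicians are not (Study design; Control group). Rivaroxaban is discontinued for unacceptable toxicity, with no dose modification (Intervention group). The Ki67 model adjusts for baseline Ki67 and for covariates such as grade and HER-2 status (Analysis, Ki67).

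**The concern.** An intention-to-treat analysis keeps every randomised patient in the arm assigned. Here the analysed set depends on what happens after randomisation: whether the patient withdraws, has the end-of-trial procedure, and yields a sample. A statistical analysis plan cannot honour both statements, so the protocol wording itself has to change.

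Replacement restores the number analysed but not the randomised comparison. Blinded reading protects the Ki67 measurement. It does not protect the decision to withdraw or to forgo the biopsy, which is made by people who know the arm. One route to leaving, drug toxicity, exists only on rivaroxaban. Patients due for neoadjuvant chemotherapy must also undergo an additional research biopsy, which is a further point at which tissue can be lost in either arm.

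If loss differs by arm and is related to Ki67, the treatment difference is biased, and a completers result would be published under the ITT label.

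**Working it through.** **1. The plan's own figure.** The inputs come from the Sample size calculation section: "The trial is designed with a two-sided alpha level of 0.05" and "an estimated 80% power to detect a 0.6 standard deviation (SD) reduction". Allocation is 1:1.

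- Normal approximation: n per arm = 2 × (1.960 + 0.842)² / 0.6² = 43.6, so 44 per arm and 88 in total, with power 80.4%.
- Exact t test: 44.6 per arm; power at 44 per arm is 79.5%.

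The stated 88 is reproduced. This point concerns the analysis population and does not dispute that figure.

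**2. The passages side by side.**

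| Event after randomisation | What the article does | What ITT requires |
|---|---|---|
| Withdraws from the trial | Removed and replaced | Kept in the allocated arm; missing Ki67 handled |
| No surgery or repeat biopsy | Removed and replaced | Same |
| No primary-endpoint sample | Replaced | Same |
| Deviates from protocol | Case by case, no criteria given | Kept in the allocated arm |
| Stops rivaroxaban but gives tissue | Not listed for removal | Kept in the allocated arm |

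The first three rows conflict with ITT. The fourth leaves a post-randomisation choice open. The fifth is compatible with ITT but is nowhere stated outright. Imputation does not resolve the first three rows, because replacement comes first and a removed patient is not imputed.

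**3. Illustration of size.** The documents give neither the loss per arm nor how removed patients differ, so both are assumptions. Let a share f of the rivaroxaban arm only be removed, and let their mean Ki67 outcome differ from that of retained patients by k SD. The mean of the whole arm is (1 − f) × retained mean + f × removed mean, so analysing only the retained patients shifts the arm mean by f × k SD. Type I error and power come from the noncentral t with 44 per arm (86 df) and noncentrality equal to the true difference plus or minus the bias, times √22. The value f = 10% is the article's overall drop-out allowance, placed entirely in one arm.

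| f | k | Bias (SD) | Share of 0.6 SD | Two-sided type I error | Power if bias is against the drug |
|---|---|---|---|---|---|
| 10% | 0.25 | 0.025 | 4% | 5.2% | 76.0% |
| 10% | 0.5 | 0.05 | 8% | 5.6% | 72.3% |
| 10% | 1.0 | 0.10 | 17% | 7.5% | 64.0% |

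Without bias, type I error is 5.0% and power is 79.5%. The planned model is a beta regression with baseline adjustment, so k should be read as the difference that remains after adjustment, and the t-test figures are a guide only.

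**4. Numbers without substitution.** Keeping 88 evaluable at 10% loss needs 88 / 0.90 = 97.8, so 98 randomised. With the planned 96, 96 × 0.90 = 86.4 are evaluable; at 43 per arm the t-test power is 78.5%.

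**The case against.** The best defence is that a trial with a tissue endpoint needs tissue, that replacement may be no more than recruiting further patients from the permuted-block lists, and that blinded reading, a short treatment window and baseline adjustment leave little room for bias. Some of this stands. Nothing in the article says that a replacement inherits the allocation of the patient removed, and nothing shows that withdrawal is related to Ki67. But the article goes beyond over-recruitment, because it takes randomised patients out of the study while calling the analysis ITT.

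Several stronger readings are tempting, and the text does not support them.

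- **That bleeding, stopping the drug or rescheduled surgery leads to removal.** The triggers are withdrawal from the trial, no procedure, or no sample. On toxicity the drug is discontinued, and the retention section mentions withdrawal from trial treatment separately. A patient who stops and still gives tissue may stay in.
- **That loss occurs only on rivaroxaban.** Controls can also withdraw or decline the research biopsy. Similar loss for similar reasons would largely cancel.
- **That people who know the allocation decide on deviators.** The retention section does not say who decides.
- **That adverse events of removed patients are lost.** Safety monitoring collects events from trial entry through follow-up. The removal wording needs clarifying, but it does not show that harm would be understated.
- **That multiple imputation would cure the problem.** Imputation by arm assumes missing at random. When only the outcome is missing and the imputation model uses the covariates already in the analysis model, it gives essentially the adjusted complete-case estimate. Bias from loss that depends on the unseen outcome remains.

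**Conclusion.** The point holds in a limited form. As written, the plan produces a completers or modified ITT set under an ITT label. This follows from the text alone and needs no assumption.

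That the Ki67 comparison can be biased follows from the open allocation and from a reason for stopping that exists in one arm only. How large the bias is, and in which direction, cannot be derived from the documents. The figures of 0.025 to 0.10 SD and 5.2% to 7.5% type I error rest on three assumptions: 10% loss, all of it in one arm, and removed patients differing by 0.25 to 1.0 SD after adjustment. Small or balanced loss would do less.

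This should be fixed. A more serious rating would need loss confined to one arm, discarded adverse events or unblinded decisions on deviators, and the article states none of these.

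**What to change.** Reconcile the Sample size calculation, Analysis and retention sections as follows.

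1. Delete the removal wording. Keep every randomised patient, including deviators, in the allocated arm, and drop the case-by-case rule as far as it touches the analysis population.
2. State that stopping rivaroxaban is not withdrawal from the trial, and that planned end-of-trial tissue and adverse events are still collected unless consent for this is withdrawn. This concerns data collection only and changes no treatment rule.
3. Treat extra patients as additional randomisations, never as substitutes. Plan about 98 randomised to keep 88 evaluable at 10% loss, or keep 96 and restate the power slightly lower (78.5% by the t test). Align the statements in the Abstract and Study design that 88 will be randomised.
4. Make the by-arm multiple imputation already named the rule for missing Ki67. Report the tissue-available analysis beside it, labelled as modified ITT or complete case.
5. Add a missing-not-at-random sensitivity analysis, for example delta-adjusted imputation with the shift allowed to differ by arm, since imputation alone does not remove bias from informative loss.
6. State that safety summaries include all randomised patients, in line with the Safety monitoring section.
7. Report withdrawals and missing tissue by arm, with reasons.

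The cost is an amendment to wording, modest extra analysis, and about two more patients than the 96 already allowed for.
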